# Ketogenic diets as an adjuvant therapy in glioblastoma (the KEATING trial): study protocol for a randomised pilot study

**DOI:** 10.1186/s40814-017-0209-9

**Published:** 2017-11-28

**Keywords:** Ketogenic diet, Modified ketogenic diet, Medium chain triglyceride diet, Glioblastoma

## Abstract

**Background:**

Glioblastoma is the commonest form of malignant brain tumour in adults, affecting 2–3 people per 100,000 per year. Despite current treatment options including surgical resection, radiotherapy and temozolomide chemotherapy, overall survival at 2 years is approximately 27%, with a median survival of 12–14 months. The ketogenic diet (KD) is postulated to work by simulating the metabolic response to fasting by promoting the utilisation of ketones as a primary energy source, and depriving the glycolytic pathways utilised by malignant glioma cells for growth. At present, there is no consensus as to which KD is preferable, with previous case series using different KDs, at different points in the treatment pathway. The aim of this randomised pilot study is to investigate protocol feasibility, tolerability and the impact on patient health and quality of life of two different KDs within an NHS setting. The results of this pilot study will inform which KD will be most deliverable and adhered to by patients in order to test for effectiveness in future trials.

**Methods:**

A prospective, non-blinded, randomised, pilot study will be undertaken in 12 patients with newly diagnosed glioblastoma treated by surgical resection. Patients will be randomised in a ratio of 1:1, using a permuted block randomisation method to one of two diets; the modified ketogenic diet and the medium chain triglyceride ketogenic diet. Primary data collection will take place 12 weeks after starting the diet and secondary data collection after 12 months. Feasibility will be assessed by retention and recruitment rates, ability to enrol patients prior to starting chemoradiotherapy, dietary compliance and adjustments, ketone levels, glucose levels and intervention time. Patient impact will be assessed through quality of life and food acceptability questionnaires, gastrointestinal side effects and changes to biochemical markers and anthropometric measures, assessed at regular intervals.

**Discussion:**

The results of this pilot study will be used to inform the feasibility, methodological design and power calculations of future phase III clinical trials investigating the effectiveness of KD as an adjuvant therapy in the management of glioblastoma.

**Trial registration:**

ISRCTN71665562 and NCT03075514.

## Background

Glioblastoma (GB) is the commonest form of malignant brain tumour in adults, affecting 2–3 people per 100,000 per year [1]. Despite current treatment options including maximal safe resection, radiotherapy and temozolomide chemotherapy [2], overall survival at 2 years remains poor (median survival of 12–14 months [3]). Several recent trials investigating newer chemotherapy agents (e.g. RTOG 0825–Bevacizumab trial [4]) and targeted therapies (e.g., CENTRIC–Celengitide trial [5]) have not resulted in any improvement to prognosis. Therefore, alternative treatment options are being explored and there is increasing clinical interest for investigating the ketogenic diet (KD) therapy as an adjuvant treatment for patients with GB.

KDs are high fat, low carbohydrate diets, resulting in the production of ketones as a primary energy source, depriving the glycolytic pathways utilised for growth by GBs. Laboratory studies of the effect of KDs in glioma mouse models have demonstrated increased survival [6], enhanced radiotherapy sensitivity [7], improved chemotherapy signalling [8] and reduced peritumoural oedema [9].

Recent studies investigating the use of the KD in humans have focused on the feasibility, safety and efficacy, in view of the fact that the diet may be considered unpalatable and unacceptable to patients with a limited life expectancy. Several small case studies [10–13] and one pilot study [14] have been reported.

Various forms of the KD have been developed over recent years to improve palatability and compliance, whilst maintaining efficacy within the diets primary evidence base of paediatric epilepsy [15, 16]. The two least restrictive KD are the modified ketogenic diet (MKD) and the medium chain triglyceride (MCT) KD, both of which are currently used for treating paediatric epilepsy within the National Health Service (NHS) and have been utilised in previous glioblastoma case series.

The MKD induces ketosis through encouraging a high fat and low carbohydrate intake, without limiting protein, fluid or energy intakes. There is no need for a fasting start or hospitalisation to commence the diet [17]. MKD is likely to be the most flexible and palatable KDs; therefore, may be more suitable for adults undergoing oncological treatments.

MCT KD was first described by Huttenlocher, Wilbourn and Signore [18] as a modification to the classic KD. It allows for the inclusion of larger portions of carbohydrate, thus, improving dietary tolerance and acceptability. A recent study by Martuscello et al. [19] investigating the use of MCT KD in GB animal models found slower tumour progression, increased survival, increased body weight and positive changes to serum lipids, in comparison to a standard KD and controls.

## Rationale

The effect of lifestyle factors (including diet) on tumours is one of the top 10 priority areas for research identified by the James Lind Priority Setting Partnership in the Neuro-Oncology community [20]. To enable an adequately powered randomised controlled trial to be undertaken, investigating the efficacy of the ketogenic diet in the therapeutic management of glioblastoma, this preliminary study is important to test protocol methodology and to explore potential impact on patient quality of life and health. At present, it is not known which KD, if any, holds promise for further investigation of effectiveness. Therefore, this study will directly compare two KD (MKD and MCT KD) to determine which diet is most deliverable and best adhered to by patients in order to test clinical effectiveness, as a primary outcome (overall survival) in a future definitive trial, within an NHS glioblastoma population. In a trial of effectiveness, a control group would be required (such as ‘healthy eating’) and directly compared to the ‘successful’ dietary arm from this pilot.

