### Sample size and recruitment

This study is being conducted as part of a PhD thesis. Twelve patients will be recruited over a 12 months period. Previous feasibility work shows this recruitment rate is achievable. Patients will be identified at a weekly neuro-oncology multi-disciplinary team (MDT) meeting; with documentation within MDT case sheet deemed an appropriate referral. Patients will be approached for recruitment after surgery and histological diagnosis of GB. Recruitment will take place for 12 months from the date of opening. Patients referred for the KEATING trial will be offered a screening appointment. A screening log will be maintained for all patients referred to the trial and reasons for ineligibility will be noted.

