### Allocation strategy

Patients will be randomised into MKD or MCT KD groups. The patients will be informed of diet group by telephone. A permuted block randomisation method will be adopted, at a 1:1 ratio using ‘sealedenvelope’™ randomisation system. This will be set up and administered by the statistician ([name]) who is not involved with the recruiting of patients.

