### Primary outcome measures

Assess retention and drop-out rates defined as:The number of patients who start randomised treatment as a proportion of the number randomised, with reasons for non-compliance.The number of patients who complete 12 weeks of diet as a proportion of the number randomised, with reasons for non-compliance.The time to dietary discontinuation (week 12 or duration to discontinuation if prior to this).A description of barriers and facilitators to data collection and participant retention will also be included.

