### Statistical considerations

#### Sample size

Feasibility data demonstrates a likely retention rate of 70% participants at 12 weeks. With a sample size of 12, we will be able to estimate retention rates of 70% to within a 95% confidence interval of ± 25.93% (Hooper [36]). Billingham et al. [37] demonstrate a median sample size of 30 (range 8–114 participants) for UK pilot studies, whilst Hertzog [38] reports on the statistical adequacy for sample sizes of 10–40, thus further justifying a sample size of 12 for the current trial.

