## Discussion

### Practical considerations

When designing the trial, we considered a number of practical issues to enable implementation within an NHS setting.

When deciding on which KDs to include within the trial, nutritional adequacy and previous evidence base were considered. There are various types of KDs, offering varying contents of fat and carbohydrate. From the literature the two KDs previous cited in oncology case series include the MKD and the MCT KD [13, 14, 39, 40]. Both diets allow for the sufficient provision of protein, essential for patients undergoing oncological treatments, in comparison to the classic ketogenic diet which would not meet adult protein requirements. Both MCT and MKD are currently used in NHS practice for patients with refractory epilepsy.

In this trial, the KD will be offered alongside current standard of care. In order to allow for future meta-analysis of data, the diet will be commenced post-surgical resection, prior to chemoradiotherapy in keeping with US centres [41, 42]. This theory is supported by previous animal models which illustrate the KD to enhance the effects of chemoradiation [6–8].

Methods for assessing ketone and glucose levels were also considered. Blood ketone and glucose levels can provide a more accurate result, when compared to urinary ketones, due to the effects of urinary dilution. However, blood monitoring is more invasive for the patient and considerably more expensive when considering trial design and potential future NHS implementation. The minimum ketone monitoring requirements cited by the International League Against Epilepsy Task Force for Diet Therapy state urinary ketones to be a minimum standard [43]. Therefore, in keeping with this, we will conduct urinary ketone monitoring, with additional weekly blood ketone and glucose levels (home finger prick testing), with a view to informing future methodology.

In terms of recruitment, 12 patients is an achievable target and suitable for a pilot study, however, an element of statistical uncertainty will be present. Therefore, we have opted for descriptive statistical methods and will apply caution when interpreting results for any future study design.

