## Conclusion

This pilot study will be the first in the UK to investigate the feasibility and tolerability of KD in GB patients. By testing protocol feasibility, we will determine which diet is most deliverable and adhered to by patients, and this will inform the methodology of future phase III clinical trials, from which effectiveness could be determined. We will also generate data on diet acceptability and the impact on patient quality of life and anthropometry.

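### The pilot is said to determine which diet is better, but its precision is worked out only for all 12 patients pooled, and about 6 per diet cannot support that claim

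*Protocol article*

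**What the plan says.** The comparative claim appears twice. The Rationale states that "this study will directly compare two KD (MKD and MCT KD) to determine which diet is most deliverable and best adhered to by patients", and adds that in a later effectiveness trial a control group would be set against the arm that succeeds here. The Conclusion repeats that "we will determine which diet is most deliverable and adhered to by patients".

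On size, the protocol says "Twelve patients will be recruited over a 12 months period" and "A permuted block randomisation method will be adopted, at a 1:1 ratio". The justification under Sample size is that "Feasibility data demonstrates a likely retention rate of 70% participants at 12 weeks" and that with 12 patients "we will be able to estimate retention rates of 70% to within a 95% confidence interval of ± 25.93" percentage points. The relevant primary outcome is "The number of patients who complete 12 weeks of diet as a proportion of the number randomised".

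Under Defining success, retention, acceptability and data completeness are graded diet by diet; only recruitment and starting the diet on time are graded on the combined arms. Practical considerations concedes that "an element of statistical uncertainty will be present" and therefore chooses descriptive methods and careful interpretation.

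**The concern.** The stated purpose is a ranking of two diets, while the sample size is justified for a single proportion in the whole group. The precision that governs the per-diet retention criterion, and the precision that governs any comparison, are not given. A reader who sees ± 25.93 points beside a promise to determine the better diet may take that figure as the accuracy behind the choice. The choice has consequences, because it settles which diet is tested in a definitive trial with overall survival as its primary outcome. If the claim is read literally, a gap of one or two patients could be reported as having settled the matter.

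**Working it through.** **Inputs.** Total of 12 patients (Sample size and recruitment). Allocation 1:1 in permuted blocks (Allocation strategy), so about 6 per diet; the block size is not stated. Retention of 70% at 12 weeks and a 95% level (Sample size). The 70% is given for participants overall; applying it to each diet is my assumption, and it is varied below.

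**1. The plan's own figure.** Wald half-width, all 12 pooled: 1.96 × √(0.7 × 0.3 / 12) = 0.2593, or ± 25.93 points. The stated figure is reproduced, and it is a pooled figure.

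**2. One diet, n = 6.** 1.96 × √(0.7 × 0.3 / 6) = 0.367, or ± 36.7 points.

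**3. Difference, 6 against 6.** 1.96 × √(2 × 0.7 × 0.3 / 6) = 0.519, or ± 51.9 points. With the same retention in both diets at other values:

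| Retention in each diet | Half-width of difference (points) |
|---|---|
| 50% | ± 56.6 |
| 70% | ± 51.9 |
| 75% | ± 49.0 |
| 80% | ± 45.3 |

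**4. A better interval for small samples.** The Wald formula is rough at n = 6, so I also took the Newcombe interval (from Wilson limits) for possible results:

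| Observed | Difference (points) | 95% interval (points) |
|---|---|---|
| 4/6 v 4/6 | 0 | -44 to +44 |
| 5/6 v 4/6 | +17 | -30 to +56 |
| 5/6 v 3/6 | +33 | -17 to +67 |

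The one-patient gap and the two-patient gap shown both leave either diet as possibly the better one.

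**5. Equal diets.** For two independent Binomial(6, 0.7) counts, the probability of a tie is the sum of squared probabilities, 0.248. The probability of a gap of at least two patients (33 points or more) is 0.341. That leaves 1 - 0.248 - 0.341 = 0.411 for a gap of exactly one patient. The probability of a gap of two or more is 0.388 at 50% retention, 0.310 at 75% and 0.267 at 80%.

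**6. Unequal diets.** Exact ranking probabilities with 6 per diet:

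| True retention | Better diet first | Tie | Better diet second |
|---|---|---|---|
| 70% v 50% | 66.8% | 17.9% | 15.3% |
| 80% v 50% | 79.9% | 12.8% | 7.3% |
| 90% v 50% | 90.8% | 6.9% | 2.2% |

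**The case against.** The strongest reply is that this is a pilot that promises no test. The primary objective under Aims and objectives is to estimate retention, the analysis is descriptive, the Abstract speaks only of informing the choice, and Practical considerations asks for caution in exactly the use that is feared here. A pilot need not be powered for a comparison. For picking a candidate, odds of 67% against 15% are moderately favourable. All of this stands, and it is why no larger sample is asked for. It does not cover the Rationale and the Conclusion, where the verb is unqualified; the Conclusion comes after the caution and does not carry it over.

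A second reply is that the choice would also draw on compliance, acceptability, dietetic time and side effects. That is fair, but each of these also rests on about 6 patients per diet.

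A reader might go further and infer that the traffic lights choose the diet, so that 5/6 (Green) against 4/6 (Amber) would discard one on a single patient. The article does not say so. Amber means review, only Red means stop, the colours grade whether to progress, and Defining success names methods for assessing problems and documenting the decision. Nor should much be made of two other figures. Equal diets at 70% show some difference in about 75% of trials, but that counts one-patient gaps, which nothing in the article treats as a trigger. Exactly one diet meets the Green retention threshold in about 49%, but retention is only one of several Green criteria.

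Finally, the form of the interval is a matter for the analysis plan that the article announces. Its absence from the article is not the fault raised here.

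**Conclusion.** The point holds as a mismatch between claim and design. The Rationale and the Conclusion say the trial will determine the better diet. With about 6 patients per diet, the retention difference is known only to about ± 52 points, and one diet's retention to about ± 37, against the ± 25.93 that the article states for the pooled group. At 70% retention, equal diets differ by two or more patients in about a third of trials. A true 20-point advantage (70% against 50%) puts the better diet first in about two thirds.

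These figures assume full recruitment, an even split, independent patients and 70% retention in each diet. The conclusion does not hang on the 70%: with equal retention between 50% and 80%, the half-width of the difference stays between 45 and 57 points. Only a very large true gap, such as 90% against 50%, would be ranked correctly about nine times in ten. The documents do not support any claim that the plan contains a rule that would drop a diet on one patient's outcome.

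**What to change.** - **Rationale and Conclusion:** replace the promise to determine which diet is better with *describe the retention and adherence of each diet to inform the choice*.
- **Sample size:** beside the pooled ± 25.93 points, add the precision for one diet (about ± 37 points) and for the between-diet difference (about ± 52 points). Say that both assume 70% retention in each diet and 6 patients per diet.
- **Analysis plan:** report the between-diet difference in 12-week completion with a Newcombe or exact 95% interval, and state that a difference of one or two patients does not by itself establish the better diet.

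The cost is a few sentences and one added interval. The article would make a more modest claim and show less favourable precision. No extra patients or visits are needed, and the success criteria stay as they are.

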## Methods

### Aims and objectives

The aim of this trial is to investigate protocol feasibility and patient impact by comparing two KDs in an NHS setting, with a view to informing the design of future phase III clinical trials. The primary objective is to estimate retention rates to inform sample size calculations of future, definitive trials. Secondary objectives in relation to protocol feasibility include estimations of recruitment, enrolment and long-term retention rates and to obtain data on dietary compliance, dietary adjustments required to achieve ketosis, ketone and glucose levels, intervention time, protocol refinements and completeness of data. Secondary objectives related to patient impact include collating data on quality of life, food acceptability, gastrointestinal side effects, biochemical markers and anthropometry.

### Design

This is a prospective, non-blinded, randomised, pilot study which will be undertaken in patients diagnosed with newly diagnosed GB. Patients will be randomised to receive one of two types of KD; MKD or MCT KD. The trial has received ethical approval from the North West–Greater Manchester West Research Ethics Committee (17/NW/0013) and has been registered with the International Standard Randomised Controlled Trial Number registry (reference number 71665562) and ClinicalTrials.Gov (reference number NCT03075514).

### Setting

This single centre pilot trial will be conducted at The Walton Centre NHS Foundation Trust (WCFT), Liverpool, UK. WCFT is a dedicated neuroscience hospital.

### Participants

The target population is adults with newly, histologically diagnosed GB. All patients considered for the trial must meet the following inclusion criteria:Age ≥ 16 years,Patient at WCFT,Performance status ≤ 2^1^ (numerical grading of patients well-being and function) [21],Confirmed histological diagnosis of GB (WHO grade IV, [22]),Undergone surgical resection and will go onto receive chemoradiotherapy with temozolomide.

Patients exhibiting the following will be excluded from the study:Having any prior use of a KD,Kidney dysfunction,Liver dysfunction,Gall bladder dysfunction,Metabolic disorder,Eating disorder (history of anorexia nervosa, bulimia nervosa, binge eating disorder),Diabetes (requiring medication),Body mass index (BMI) ≤ 18.5 kg/m^2^,Use of weight loss medications,Currently pregnant,Performance status ≥ 3 [21].

### Sample size and recruitment

This study is being conducted as part of a PhD thesis. Twelve patients will be recruited over a 12 months period. Previous feasibility work shows this recruitment rate is achievable. Patients will be identified at a weekly neuro-oncology multi-disciplinary team (MDT) meeting; with documentation within MDT case sheet deemed an appropriate referral. Patients will be approached for recruitment after surgery and histological diagnosis of GB. Recruitment will take place for 12 months from the date of opening. Patients referred for the KEATING trial will be offered a screening appointment. A screening log will be maintained for all patients referred to the trial and reasons for ineligibility will be noted.

### Allocation strategy

Patients will be randomised into MKD or MCT KD groups. The patients will be informed of diet group by telephone. A permuted block randomisation method will be adopted, at a 1:1 ratio using ‘sealedenvelope’™ randomisation system. This will be set up and administered by the statistician ([name]) who is not involved with the recruiting of patients.

### Intervention design

All participants will be invited to attend clinical consultations pre-diet, on initiating diet, 6 weeks from initiation, 12 weeks from initiation (primary completion) and every 3 months for a total of 12 months (secondary completion) or until dietary discontinuation if prior to this. Telephone consultations will take place post initiation at weeks 1, 3 and 9 to enable dietary ‘fine tuning’ (Table 1 and Fig. 1). All consultations will be undertaken with the same research dietitian. It is not possible to blind the participants or the investigators due to differences between the diets and dietary education required.

**Table 1 Tab1:** Study schedule

	Study period										
		Enrolment/diet allocation	Post allocation (on diet)								Close out
Timeline		1 week post-histology	1 week after clinic 1	1 weeks after clinic 2	3 weeks after clinic 2	6 weeks after clinic 2	9 weeks after clinic 2	12 weeks after clinic 2	6 months after clinic 2	9 months after clinic 2	12 months after clinic 2
Visit window	Post-histology	± 5 days	± 5 days before radiotherapy	± 3 days	± 3 days	± 5 days	± 3 days	± 5 days	± 10 days	± 10 days	± 10 days
Clinic visit	Telephone discussion	Clinic appointment 1 Consent, register, baseline assessment, randomisation	Clinic appointment 2 Commence diet	Telephone review 1	Telephone review 2	Clinic appointment 3 Diet review	Telephone review 3	Clinic appointment 4 Diet review	Clinic appointment 5 Diet review	Clinic appointment 6 Diet review	Clinic appointment 7 Diet review End of trial
Information sheet	X										
Informed consent		X									
Eligibility screen		X									
Randomisation		X									
Medical history review		X									
Medications review		X									
Anthropometry		X				X		X	X	X	X
Biochemistry		X						X	X	X	X
Food diary		X				X		X	X	X	X
Ketone diary						X		X	X	X	X
Quality of life (QoL) questionnaire EORCT QLQ C30		X				X		X	X	X	X
QoL questionnaire QLQ BN20		X				X		X	X	X	X
Food Acceptability Questionnaire		X				X		X	X	X	X
Dietary review		X	X	X	X	X	X	X	X	X	X
Ketone review				X	X	X	X	X	X	X	X

X = procedure carried out

